### Study Population

#### Inclusion and Exclusion Criteria

Workers aged 19 to 59 years with a BMI of ≥23 kg/m^2^ (overweight or obese), ready to participate in the intervention (assessed through readiness to participate in screening), and providing informed consent were included in this study.

Workers who (1) had recent involvement in weight loss program or activity (IF, diet changes, or physical activity changes or any activities that were performed constantly to reduce weight); (2) were affected by any eating disorder; (3) were diagnosed with diabetes and hypertension (on medication) or other metabolic health disturbances such as thyroid disease, chronic kidney disease, malignancy, and polycystic ovarian syndrome; (4) were taking any medication or supplements that can affect study outcome; (5) were pregnant; and (6) had lack of capacity or language skills to independently follow the protocol were excluded from this study.

#### Sample Size

Sample size calculation was conducted using a power and sample size program. It followed the rules required for comparison between the 2 groups [13]. The sample size was estimated using the level of significance (α=.05) and power of the study (1-β=.80), minimum suggested difference (delta) of 5% (SD 10%) weight loss that may be achieved under this intervention, and the corresponding differences among groups. The assumption of 5% weight loss used in the sample size calculation was based on a review conducted by Ryan and Yockey [14], which stated that a minimum weight loss of 5% is needed to improve cardiometabolic risk such as hypertension, diabetes mellitus, and hyperlipidemia. The minimum sample size required for this study was 64 participants. Considering 40% attrition, the required sample size for each arm was 90 participants. A total of 180 participants were required for this study.

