### Data Analysis

Analysis was conducted using the SPSS software (version 25; IBM Corp). Data for continuous variables were presented as mean (SD) or as median (IQR) for nonnormally distributed data. For categorical variables, frequencies were calculated and are presented as percentages. Variables were compared using the independent 2-tailed *t* test or Mann-Whitney *U* test for continuous variables and the chi-square or Fisher exact (n≤5 in any cell) test for categorical variables. All statistical tests were 2-sided, and the significance level was set at *P*<.05. In further analysis, repeated measures ANOVA will be used to compare the within- and between-group changes in the outcomes, adjusted for possible confounders such as age, ethnicity, and gender.

Data from the FGDs were analyzed using thematic analysis. Interviews transcribed verbatim were independently read by a qualitative researcher ([name]) to identify the preliminary codes. An interpretivist approach was taken to interpret and code participants’ experiences for the entire study. In this way, the coding of participants’ feedback was performed without assumptions or subjective interpretation by the researchers. Meaning units were reviewed, identified, and sorted into codes, before grouping them into categories. Finally, through consensus, the content of each category group was summarized and grouped into main themes. The best representative participants’ quotes for each theme were chosen to support the results. Thematic analysis was used, where initial open codes were generated from the data, after which the codes were organized into larger themes.

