## Results

### Study Participants

A total of 302 volunteers were interested in joining the study and underwent the screening process. After screening for BMI and eligibility during the first stage of recruitment, of 302 volunteers, only 203 (67.2%) were found eligible. Most volunteers were excluded owing to a BMI of <23 kg/m^2^ or having chronic diseases on medication, such as diabetes mellitus and hypertension. During the readiness to participate in screening (stage 2 recruitment phase), 27 volunteers were excluded for various reasons but were not limited to reasons such as commitment issues, furthering education, or moving away. Hence, there were a total of 177 participants recruited in this study; 91 (51.4%) in the IFHP group and 86 (48.6%) in the HP group (Figure 1). During the supervised intervention period, 28 participants withdrew from our study in both groups (IFHP: 16/28, 57%; HP: 12/28, 43%), whereas 27 withdrew during the unsupervised period (IFHP: 12/27, 44%; HP: 15/27, 56%). The reasons for withdrawal included pregnancy (13/55, 24%), inability to commit to study intervention (24/55, 44%), transfer to a different workplace (8/55, 15%), being diagnosed with hypertension, diabetes, hypercholesterolemia on medication (5/55, 9%), and other reasons (5/55, 9%). There were 63 and 59 participants who completed the study in the IFHP and HP groups, respectively.

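### A sample of 90 per arm does not keep 80% power at 40% attrition: 64 evaluable per arm would need 107 enrolled

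*Protocol article*

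**What the plan says.** The Sample Size section describes a two-group comparison ("It followed the rules required for comparison between the 2 groups") with alpha .05, power .80 and a "minimum suggested difference (delta) of 5% (SD 10%) weight loss that may be achieved under this intervention". The Data Analysis section adds the sidedness: "All statistical tests were 2-sided, and the significance level was set at" P<.05.

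From these inputs the Sample Size section reports: "The minimum sample size required for this study was 64 participants". The next sentence applies the allowance for loss: "Considering 40% attrition, the required sample size for each arm was 90 participants". The section then gives 180 as the total. It prints no inflation formula.

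The Study Participants section of the Results reports 177 recruited (91 IFHP, 86 HP), with 28 withdrawals in the supervised phase (16 IFHP, 12 HP) and 27 in the unsupervised phase (12 IFHP, 15 HP). It concludes: "There were 63 and 59 participants who completed the study in the IFHP and HP groups, respectively".

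**The concern.** An attrition allowance should ensure that, after the assumed fraction of enrolled participants has been lost, the required evaluable number remains. That means dividing by the retained fraction. Here 60% of 90 is 54, which is 10 short of the 64 that the same paragraph says is needed. The paragraph therefore claims 80% power and tolerance of 40% attrition together, and 90 per arm does not deliver both.

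This paragraph is the article's only justification for the study's size. Because observed attrition was below 40%, a reader would naturally conclude that the planned power was preserved at month 6. It was not quite preserved.

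There is also a smaller fault of wording. The sentence giving 64 reads as a total for the study, although the calculation and the sentence after it show that 64 is per arm.

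**Working it through.** **Inputs**

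| Quantity | Value | Source |
|---|---|---|
| Difference, SD | 5, 10 (d = 5/10 = 0.5) | Sample Size |
| Alpha, power | .05, .80 | Sample Size |
| Sidedness | two-sided | Data Analysis |
| Allocation | 1:1 | Sample Size (90 per arm, 180 in total) |
| Attrition | 40% | Sample Size |
| Recruited | 91 and 86 | Study Participants |
| Completers | 63 and 59 | Study Participants |

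**1. The 64 reproduces, per arm.** The normal approximation is n = 2(1.960 + 0.842)² / 0.5² = 62.8, so 63 per arm. The two-sample t test gives 63.8, so 64 per arm, which is the stated figure. A one-sided test would give about 50, so the two-sided reading is the right one. If 64 were a study total (32 per arm), power would be only about 50%, which rules that reading out.

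**2. The 90 reproduces only by multiplication.**

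- n × (1 + attrition) = 64 × 1.4 = 89.6, so 90. This matches.
- n / (1 − attrition) = 64 / 0.6 = 106.7, so 107. This does not match.

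Starting from 63 instead of 64 does not help: division gives 105 and multiplication gives 89.

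**3. What 90 per arm delivers at 40% attrition.** 90 × 0.6 = 54 evaluable per arm. Power for d = 0.5, two-sided alpha .05, is 73.1% by the t test (73.8% by the normal approximation). For comparison, 64 per arm gives 80.1%.

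**4. What 90 per arm can absorb.** The largest loss that still leaves 64 is 1 − 64/90 = 28.9%.

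**5. What 40% attrition requires.** 107 per arm, 214 in total. The shortfall against the plan is 107 − 90 = 17 per arm, or 34 in total.

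**6. What happened.** Overall loss was 55/177 = 31.1% (IFHP 28/91 = 30.8%; HP 27/86 = 31.4%). t-test figures for a difference of 5 with SD 10:

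| Time point | Remaining (IFHP, HP) | Power |
|---|---|---|
| Month 3 | 91 − 16 = 75, 86 − 12 = 74 | 86% |
| Month 6 | 63, 59 | 78.2% |

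At month 6 the difference detectable with 80% power is 5.1 points.

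**The case against.** The strongest case on the other side accepts the arithmetic and disputes its importance.

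- **The realised effect is small.** At month 6 the design had 78% power instead of 80%, and a detectable difference of 5.1 instead of 5.0 points. That would hardly change how anyone reads a null result. The 73% figure needs a 40% loss that did not occur. This stands, and the consequence should be put modestly.
- **Month 3 is unaffected.** The article does not tie the calculation to a time point, and after the supervised phase 75 and 74 participants remained, above 64 in both arms. This also stands: the shortfall belongs to month 6 only.
- **Part of the shortfall is recruitment.** HP enrolled 86 instead of 90. At the observed HP loss, 90 enrolled would have left 90 × 59/86 = 61.7, about 62. This is true, but 62 is still below 64, and IFHP ended at 63 despite enrolling 91.
- **The formula is inferred.** The article does not print 64 × 1.4. That is correct, but the contradiction does not depend on the route, since 90 × 0.6 = 54 however 90 was reached.
- **The planned analysis differs.** Repeated measures ANOVA adjusted for age, ethnicity and gender is planned, whereas these powers are for an unadjusted t test on independent participants. Any power quoted should say so.

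Could attrition have been meant as 40% of the evaluable number? Nothing in the article defines it that way, and the Study Participants section counts withdrawals among those recruited.

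**Conclusion.** The concern holds. On the article's own inputs, 90 per arm with 40% attrition gives 54 evaluable per arm and 73% power, not 80%. The stated attrition would have needed 107 per arm (214 in total), and 90 per arm covers about 29%.

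The observed loss of 31.1% fell between those two limits. As a result, attrition was within plan, yet both arms ended month 6 below the required 64. The practical cost was about 2 percentage points of power at month 6 and none at month 3. This is an error of statement that should be corrected because it is false as written, not because it undermines the study's results.

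These figures assume a two-sided two-sample t test, SD 10, attrition as a fraction of those enrolled, and independent participants. They make no allowance for allocation by institute.

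**What to change.** Do not enrol more participants; restate the figures in the Sample Size section. Suggested text:

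> A minimum of 64 evaluable participants per arm was required. The target of 90 per arm allows for about 29% attrition. At 40% attrition, 107 per arm (214 in total) would have been needed, and 90 per arm gives 73% power. With the 63 and 59 participants who completed month 6, power for a 5-point difference (SD 10) is 78%. Powers are for an unadjusted two-sided two-sample t test and ignore allocation by institute.

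The essential part is the first three sentences. The power at the achieved numbers is a useful addition, provided the caveat stays with it.

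The cost is a few sentences and a slightly less favourable stated figure. No analysis or study procedure changes.

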### Dietary Protocols

The combined IFHP regimen consisted of dry fasting from dawn to dusk for 2 days a week (Mondays and Thursdays) and practice of HP for the rest of the week. During the fasting days, the participants were encouraged to have a meal before dawn. No food or drink was allowed after dawn (approximately 13 hours) until sunset. They did not need to follow an HP diet on the fasting day. Smoking and sexual activity were also forbidden during the fasting day, following the Sunnah fasting obligation. Fasting adherence records were taken as 0, 1, or 2 fasting day or days per week. For the rest of the week, they were obligated to consume meals according to the HP concept. The female participants were discouraged from fasting during menstruation.

Participants in the HP group were asked to practice the HP concept daily: division of plate portions into a quarter for protein, a quarter for complex carbohydrates, and a half for fruits and vegetables. Participants were advised to practice HP for all 3 main meals per day. However, the practice of at least one HP meal per day is considered the minimum requirement for adherence to the dietary protocol. The research assistants ([name] and [name]) monitored the intervention through a daily record of food intake picture (one meal per day) and a weekly fasting record.

### Study Phases

#### Recruitment Phase

The recruitment of participants for this study comprised two phases: (1) health screening and (2) readiness to participate in screening. An invitation to participate in the study was sent through Google Forms, emails, and phone calls. Volunteers were screened for inclusion and exclusion criteria by the study team. Those eligible were screened again for readiness to participate, which was conducted through face-to-face interviews. During the interviews, the participants’ readiness (motivation, willingness to commit, and enthusiasm) was assessed by a trained psychologist from the Institute for Health Behavioral Research. Only participants deemed ready to commit were included in the study. Informed consent, as well as a behavioral contract, was signed by each enrolled participant after being clearly explained the purpose of each document in the research. Both researchers and participants were unblinded to the intervention.

#### Intervention Phase

The overall duration of the intervention phase was 6 months, with 12 weeks in the supervised phase, followed by 12 weeks in the unsupervised phase. During the supervised phase, the participants started the diet protocol according to the designated intervention group. In the IFHP group, participants were reminded to fast, through a message sent to their mobile phones on the eve of fasting days, and accomplishments were recorded twice weekly. Participants in both groups were required to send a picture of one of their meals to the research assistant. In contrast, no fasting reminder, weekly fasting records, or meal pictures were sent during the latter unsupervised phase.

### Study Procedure

#### Quantitative Method

##### Data Collection

During the 6-month study duration, data collection was conducted at 3 points: baseline (before starting the supervised phase), month 3 (at the end of the supervised phase), and month 6 (at the end of the unsupervised phase). Participants were asked to answer questionnaires on social demography (during baseline only), the Food Frequency Questionnaire (FFQ), the International Physical Activity Questionnaire-Short Form (IPAQ-SF), and the Obesity and Weight-Loss Quality of Life (OWLQOL) Questionnaire. Anthropometry measurements and fasting blood samples were taken. Oral glucose tolerance test and body composition analysis were also performed.

##### Self-administered Questionnaire

The FFQ was used to determine the frequency of food and beverage consumption over the previous month. The questionnaire consisted of questions covering the frequency of cereals and cereal products, fast food, meat and meat products, fish and seafood, eggs, legumes and legume products, milk and milk products, vegetables, fruits, drinks, alcoholic drinks, confectionaries, bread spreads, and flavor intake. The validated Malay version of the FFQ used in this study consisted of 165 items, and the participants required approximately 30 minutes to answer the questions at each point of data collection [15]. The records were analyzed using Nutritionist Pro Nutrition Analysis Software 7.8.0 (Axxya Systems, 2021) to determine their energy and macronutrient intake.

To measure the quality of life, a validated Malay version of the OWLQOL questionnaire was used. The OWLQOL is a self-administered questionnaire that assesses participants’ feelings about obesity and their efforts in weight loss [16]. The 17 OWLQOL items consist of 7-point scale responses ranging from 0 (*not at all*) to 6 (*a very great deal)*. The score for each item was reversed before the total score was obtained. Consequently, it was transformed to a scale of 0 to 100, with a higher score indicating better quality of life [17]. The Malay version of the questionnaire has been validated among 28 female health staff with overweight and obesity, with a Cronbach *α* of .953 [18]. The participants needed approximately 10 minutes to complete the questionnaire.

The IPAQ-SF was used to measure the participants’ physical activity in the past week. The questionnaire was validated for use by adults in 12 countries [19]. In this study, we used the Malay version of the IPAQ-SF, which was validated in a study using data obtained from the NHMS 2011 [20]. The participants were requested to record how many days in the past week they spent on specific activities (vigorous and moderate activities and walking) for at least 10 minutes and the amount of time (in minutes) they engaged in a particular activity on an ordinary day. Physical activity level was calculated as the energy expenditure or metabolic equivalent task (MET) minutes per week (MET-minutes per week) based on the IPAQ scoring protocol [21]. To obtain MET scores for each activity, the total minutes spent on vigorous activity, moderate-intensity activity, and walking over the last 7 days were multiplied by 8.0, 4.0, and 3.3, respectively. The total physical activity score was calculated as the sum of all the MET scores from the 3 activity groups. Physical activity can also be categorized into low, moderate, and high physical activity levels, based on the scoring protocol available in the IPAQ website guidelines [21].

Sedentary behavior was also measured in this study. The question used to measure sedentary behavior was included in the IPAQ-SF questionnaire, based on the IPAQ sitting question. Participants were asked to state the total time they spent (hours) sitting or lying down, whether in the workplace, at home, or while traveling, excluding the time spent sleeping, on a typical day. The total daily sitting time was used as an indicator of sedentary behavior.

##### Anthropometric Measurements

Body weight and height were measured using a seca electronic column scale (SECA GmbH and Co KG) in kilograms and centimeters to the nearest 0.1 kg and 0.1 cm, respectively. Body weight was measured in light clothing, and participants were asked to remove their outer garments and shoes. BMI was calculated by dividing weight by height squared (kg/m^2^). As only participants with overweight and obesity were included, we categorized them into overweight (23.0-27.4 kg/m^2^), preobese (27.5-32.4 kg/m^2^), obese class I (32.5-37.4 kg/m^2^), and obese class II (≥37.5 kg/m^2^), based on the cutoff points for public health action for Malaysia [22].

Waist and hip circumferences were measured using a SECA measuring tape (SECA), to the nearest 0.1 cm with the participant standing. Waist circumference was measured at the midpoint between the top of the iliac crest and the lower margin of the last palpable rib, whereas hip circumference was measured at the widest diameter around the buttocks. The waist-to-hip ratio was calculated by dividing the waist measurement by the hip measurement. On the basis of the World Health Organization cutoff points, waist-to-hip ratio of ≥0.90 cm (men) and ≥0.85 cm (women) are abnormal, and the risks of metabolic complications substantially increased beyond these points [23].

Blood pressure was measured using an automated upper arm device (Omron Automated Blood Pressure Monitor; HEM 7130). Body composition parameters such as fat mass and fat-free mass were measured using a tetrapolar bioimpedance multifrequency InBody 770 analyzer (Biospace). Personal profiles (age, height, weight, and sex) were entered upon measurement reading.

For each parameter measured 2 measurements were taken, and the average of the 2 measurements was calculated to minimize the measurement error.

##### Biochemical Testing

Before blood collection, all participants were required to fast overnight for approximately 8 to 10 hours. Approximately 15 ml of fasting venous blood was taken from participants by the medical officers for standard biochemical tests such as fasting blood glucose, hemoglobin A_1c_, fasting insulin, and fasting lipid profile such as triglycerides, total cholesterol, high-density lipoprotein cholesterol, and low-density lipoprotein (LDL) cholesterol. The oral glucose tolerance test was performed by asking the participant to drink a 250-mL solution that consists of 75 g of glucose, and another 5 mL of venous blood was collected 2 hours after the oral glucose tolerance test.

Blood samples were processed within 2 hours, and aliquots of serum or plasma samples were stored at −20 °C before analysis. Excess blood samples will be stored for up to 20 years and will be used for future research, as clearly stated in the consent form. The hemoglobin A_1c_ level was determined by cationic exchanged high-performance liquid chromatography (Adams A_1c_ HA-8160; Arkray Inc) following the National Glycohemoglobin Standardization Programme Guidelines.

Fasting plasma glucose, triglycerides, total cholesterol, high-density lipoprotein cholesterol, and LDL cholesterol were analyzed using an automated analyzer (Dirui CS-400) with reagents purchased from Randox Laboratories. Consent was obtained from the participant for permission to extract DNA or RNA and store the remaining samples at −80 °C for future biomarker research related to obesity.

##### DNA Extraction

Genomic DNA was isolated from frozen peripheral blood samples using the QIAamp Blood Mini Extraction Kit, according to the manufacturer’s protocol (Qiagen). Briefly, 20 µL QIAGEN Protease will be added in 200 µL of blood sample, followed by 200 µL Buffer AL. The mixture was vortexed thoroughly and incubated at 56 °C for 10 minutes. Later, 200 µL of absolute ethanol will be added to the mixture before being transferred to a QIAamp Mini spin column and centrifuged at 8000 rpm. Next, 2 washing steps will be performed using washing buffers AW1 and AW2. Finally, 100 µL of distilled water will be added and incubated at room temperature for 1 minute followed by centrifuging at 8000 rpm for 1 minute to elute the DNA. The quality and quantity of the extracted DNA will be quantified using NanoDrop before being stored at −20 °C for future use.

#### Qualitative Method

The FGDs were conducted after month 6 of the study to explore the experience the participant went through, including the enablers and barriers that led to their weight loss outcomes, and obtain their insights on how to improve the intervention.

A trained psychologist from the Institute for Behavioral Research conducted the FGDs using a predetermined outlined interview guide with probes. An audio recorder was used to record conversations and for transcription. Each FGD took approximately 60 to 90 minutes to complete. In total, 4 groups were involved in the FGD, in which 2 groups consisted of participants who successfully reduced weight by at least 4% from their baseline weight, whereas the other 2 groups were among those who did not meet the requirements for weight loss as predetermined by the study parameters.

A summary of the study outcomes, based on part of the study, is listed in Table 1.

**Table 1 table1:** Summary of measurements undertaken within Cardiometabolic and Anthropometric Outcomes of Intermittent Fasting study and their associated outcome variables.

Measurements^a^		Time points				Instrument		Number of measures at each time point		Outcome variables
		Baseline	Month 3	Month 6						
